### Sample size

Sample size calculations were done using the G-power 3.1.9.2 software (developed by the University of Düsseldorf, Germany). An effect size of 0.8 and a two-sided alpha level of 0.05 were set based on the differences of pre- and post-treatment repeated measurement points of Star Excursion Balance Test (SEBT) and CAIT; a total sample of 56 participants (28 patients in each group) is required to achieve 90% power. The estimated withdrawal rate was 10–20%, and a total of 68 participants (34 patients in each group) were planned to be enrolled in this clinical trial. The power analysis is based on the primary outcome variable, including within-group differences in SEBT and CAIT (dependent variables) before and after treatment. The means and standard deviations of the SEBT and CAIT are based on the results from a similar published study from Spain (18) and preliminary experiment of the research group (intervention group: ▴SEBT-posteromedial M = 6.46, SD = 6.89, ▴CAIT M = 10.8, SD = 2.21, control group: ▴SEBT-posteromedial M =0.64, SD = 3.86, ▴CAIT M =0.2, SD = 2.10), with a 1:1 allocation ratio.

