## Patient-reported outcomes

### Cumberland ankle instability tool

The Cumberland Ankle Instability Tool (CAIT) (22) is used to focus on the severity of functional problems in patients with ankle instability, which is recommended by the International Ankle Consortium. It consists of nine items and is scored on a 30-point scale. Previous research shows that the Chinese version of CAIT is a valid and reliable questionnaire tool to evaluate ankle function in clinical trials. CAIT scale can distinguish between patients with and without CAI. A higher response score represents a better level of overall function and ankle stability, and values ≤ 25 represent ankle instability. According to a recent study, the minimum detectable change score of CAIT is ≥3, which can be used to determine the effectiveness of CAI interventions. Thus, in this study comparisons of CAIT scores before and after treatment are used as the primary outcome measure of functional improvement in patients with FAI.

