### Static balance

In this study, TecnoBody ProKin (ProKin Software Stability, TecnoBody S.r.l., Dalmine, 24044 Bergamo, Italy) will be used to evaluate the static postural control ability of the affected side's foot in patients with FAI. Subjects will be asked to stand on a balanced platform and pressure sways in all directions will be detected. First, subjects will be instructed to look directly at a front screen surface, and then they will be asked to try to maintain their balance on both the legs for 60 s, initially with their eyes open and then closed. Subsequently, patients will be asked to try to maintain their balance for 60 s on the affected side leg for 60 s with their eyes open and then closed. We will obtain the change of center of pressure (COP) of the lower limbs from the subjects. Among these, the static balance ability indexes include the length (mm) and average speed (mm/s) of body sway [total and along the anteroposterior (AP) and mediolateral (ML) axis] and area of body sway (area of the ellipse; mm^2^).

The total length of body swing (perimeter; mm) was calculated as the total length of the distance the center of gravity movement route recorded by the system during the subject's body swing, reflecting the total distance and shaking degree of the center of gravity of the human body. The greater the value, the worse the stability. Area of body sway (area of the ellipse; mm^2^) refers to the area of the center of gravity movement of the human body. The larger the area, the worse the stability.

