### Dynamic balance

This study will use a posturographic balance platform to perform dynamic balance tests to evaluate proprioception. The ProKin used in this study is an advanced technology that combines classic tilting platform connected to monitors and speakers. By creating visual and audio feedback, it can respond to the minimum movement of the platform on all planes (25). The movable balance platform in this system can detect balance measurement in all directions with an operating angle of 15°C. The index of dynamic balance ability is the total offset index, which refers to the angle between the position of the patient's overall offset and the vertical midline. The average trace error (ATE) was calculated for the proprioception index. ATE = (track length traced by the patient's ankle foot control cursor – ideal track length)/ideal track length. The greater its value, the worse the posture control ability. Also, 0–35% of ATE is considered very good, 35–100% is considered sufficient, and >100% is considered to indicate problems in proprioceptive control (26).

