### Data analysis

Statistical analysis will be carried out using SPSS Statistics, version 22.0 (SPSS Inc., Chicago, IL, USA). All assigned subjects with available data will be analyzed according to the intention-to-treat principle. Continuous variables, such as CAIT score, age, and disease duration, will be expressed as mean ± standard deviation (SD) or medians (25th to 75th centiles), depending on whether the distribution of variables is normal or skewed. For other categorical data, we will use Mann–Whitney test, chi-square test, or Fisher's exact test for statistical analysis as appropriate. Multiple-measure variables will be analyzed by repeated-measures ANOVA. Additionally, we will use the last-observation-carried-forward method to deal with the missing data. Statistical significance will be assessed as *p* < 0.05.

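### The trial is powered on a primary outcome of SEBT and CAIT, but SEBT is never scheduled or measured, no measured postural variable is designated or powered, and the stated sample-size basis does not reproduce

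*Protocol article*

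**What the plan says.** All references are to the protocol article.

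- **Sample size.** The power analysis rests on the "primary outcome variable, including within-group differences in SEBT and CAIT (dependent variables) before and after treatment". The section gives planning means and SDs for the change in SEBT (posteromedial direction) and in CAIT, in both arms. It then says: "An effect size of 0.8 and a two-sided alpha level of 0.05 were set"; "a total sample of 56 participants (28 patients in each group) is required to achieve 90% power"; and "The estimated withdrawal rate was 10–20%, and a total of 68 participants (34 patients in each group) were planned to be enrolled".
- **Cumberland ankle instability tool.** Only CAIT is given primary status: "comparisons of CAIT scores before and after treatment are used as the primary outcome measure of functional improvement".
- **Table 1.** The scheduled assessments are static balance tests, dynamic balance tests, CAIT, AOFAS-AHES and SF-36. SEBT has no row.
- **Static balance and Dynamic balance.** Both sections describe ProKin platform tests only. On the static side, "the static balance ability indexes include the length (mm) and average speed (mm/s) of body sway", together with sway area. On the dynamic side, "The index of dynamic balance ability is the total offset index", to which average trace error is added. None of these is called primary or ranked.
- **Study design and setting.** The objective has two parts, postural balance and subjective feelings of instability. The trial is described as exploratory.
- **Data analysis.** Repeated measures go to repeated-measures ANOVA, and one threshold is given: "Statistical significance will be assessed as" p < 0.05.

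**The concern.** The Sample size section and the CAIT section give two different primary outcomes, and one of the two variables in the first is not collected anywhere in the plan. This is a contradiction within the document. An analysis plan cannot repair it, because it cannot supply data that the assessment schedule does not gather.

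Two things follow. The postural half of the objective has no designated measure: the one postural variable used to size the trial is a test that is not performed, and none of the platform measures that are performed has taken its place. And once SEBT is set aside, the effect size loses one of its two stated sources, so the basis for the 68 participants has to be rebuilt on a variable that exists.

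**Working it through.** **1. Where SEBT appears.** Sample size: yes, as part of the primary variable, with planning values. Abbreviations: yes. Abstract (outcome measures), Table 1, Outcome measurements, Patient-reported outcomes, Static balance, Dynamic balance: no. CAIT appears in Sample size, in Table 1 at all three time points, and in its own section as primary.

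**2. Reproducing 28 per group.** Inputs from Sample size: d = 0.8, two-sided alpha 0.05, 90% power, 1:1 allocation.

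- Two-sample test, normal approximation: n = 2(1.960 + 1.282)² / 0.8² = 32.8, so 33 per group. The exact t-test gives 33.8, so 34 per group (68 analysed).
- Power at 28 per group: 0.8 × √(28/2) = 2.99, and Φ(2.99 − 1.96) = 84.9%. The exact t-test gives 83.6%.
- One-sided two-sample t-test: 27.5, so 28 per group, with 90.5% power.
- Paired (within-group) t-test: 19 two-sided, 15 one-sided.

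Of these variants, only the one-sided two-sample test returns the stated 28. That contradicts the two-sided alpha in the same section.

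**3. Withdrawals.** 56/0.90 = 62.2, so 63; 56/0.80 = 70. The planned 68 lies inside that range and corresponds to a loss of about 17.5% (28/0.825 = 33.9, so 34). This step is consistent. If 34 analysed per group were required instead, enrolment would be 34/0.90 = 37.8, so 38, to 34/0.80 = 42.5, so 43 per group (76 to 86 in total).

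**4. Source of d = 0.8.** From the planning values in Sample size, with pooled SD = √((SD₁² + SD₂²)/2):

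| Variable | Difference in change | Pooled SD | Between-group d | Within-group d, intervention arm |
|---|---|---|---|---|
| SEBT | 6.46 − 0.64 = 5.82 | √((6.89² + 3.86²)/2) = 5.58 | 1.04 | 6.46/6.89 = 0.94 |
| CAIT | 10.8 − 0.2 = 10.6 | √((2.21² + 2.10²)/2) = 2.16 | 4.92 | 10.8/2.21 = 4.89 |

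None of the four equals 0.8.

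**5. How many platform indices could stand for postural balance.** Static balance describes two stances (both legs, affected leg), each with eyes open and closed: 4 conditions. If the total/AP/ML bracket covers both length and speed, each condition yields 3 + 3 + 1 = 7 indices. If it covers speed only, each yields 1 + 3 + 1 = 5. Adding the two dynamic indices gives 4 × 7 + 2 = 30 or 4 × 5 + 2 = 22. Each static trial lasts a fixed 60 s, so average speed is length divided by 60. On the wider reading, 3 × 4 = 12 indices therefore repeat another one exactly. Many of the rest will be correlated.

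**The case against.** **CAIT survives.** It has planning values, is named primary in its own section and is scheduled throughout. A reader might infer that the powered endpoint as a whole cannot be analysed. The documents do not support that: only the SEBT component is lost. Nor do they rank postural balance above subjective instability; the objective names them together.

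**Multiplicity belongs elsewhere.** A reader might also infer that the platform indices, each tested at p < 0.05, make a false positive balance finding close to certain. That goes too far. Repeated-measures ANOVA is planned, so a separate test at each visit cannot be assumed. The indices overlap heavily and cannot be treated as independent. The count of 30 is one reading; it is 22 on another, and 16 if only the affected-leg stance is an outcome (2 × 7 + 2). The trial is labelled exploratory, and a multiplicity rule may sit in an analysis plan not seen here. All of this stands, so the absence of an adjustment rule is not part of this point.

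**An effect size of 0.8 is cautious.** It is smaller than either value implied by the planning data, which in itself protects the trial. That is fair, but the section presents it as derived from those data, and it is not. Caution in d also does not explain the gap between 84% and 90% at the stated d.

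**What remains.** The exploratory label does not reconcile two different primary outcomes, and condensing an article does not explain the omission. Table 1 lists the secondary scales one by one but leaves out a test used to size the trial.

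**Conclusion.** The point holds as an internal contradiction. The Sample size section includes SEBT in the primary outcome; the schedule and the outcome sections do not measure it; the CAIT section names CAIT alone. The SEBT part of the powered outcome cannot be analysed as planned, and no measured postural variable is designated or powered.

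The stated sample size does not follow from its own inputs. At d = 0.8 and two-sided 0.05, 28 per group gives 83.6% power, and 90% needs 34 analysed per group. The d of 0.8 has no visible derivation.

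This rests on the article's text and Table 1 being a complete list of assessments; the flow diagram (Figure 1) could not be read. The power figures assume a two-sample t-test on change. No SD is given for any ProKin index, so the power for a postural outcome cannot be computed from the documents.

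**What to change.** 1. **One primary outcome.** Remove SEBT from the primary outcome and reconcile the two sections: the single primary outcome is CAIT at the post-intervention assessment (week 13), TCC versus CBT. The present within-group wording should go, because the trial's question is comparative. If SEBT is in fact being collected, add it to Table 1 and to the outcome sections and rank it against CAIT.
2. **One main postural outcome.** Name one already-collected ProKin index, with its stance, eye condition and time point. Do this in a dated amendment while the statisticians are still blinded, since the stated recruitment start (5 November 2022) precedes any such change. Label the other platform indices exploratory, and keep only one of length and average speed. Which index to choose is for the investigators.
3. **Restate the sample-size basis.** Give a CAIT difference and SD for TCC versus CBT and derive d from them. The planning control-arm CAIT change of 0.2 should not simply be carried over, because the protocol's own hypothesis is that CBT also improves. If d = 0.8 is kept, justify it and either state about 84% power for 28 analysed per group or plan for 34 analysed per group.

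**Cost.** Protocol wording, no new visits or tests under the first option, and a less favourable stated power. Keeping 90% power at d = 0.8 would instead mean enrolling 76 to 86 participants at the protocol's 10–20% withdrawal. The remaining balance indices could no longer carry a confirmatory claim.

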As far as we know, only one research group has reported that TCC intervention has a positive effect on postural control and self-reported instability feeling in patients with CAI but failed to compare the clinical effects with other training programs (18). Moreover, there is no literature directly examining the comparative effects of TCC intervention and conventional balance training (CBT) protocols regarding their impact on postural stability and self-reported outcomes in patients with FAI. From the perspective of clinical utility, it is extremely interesting to see which intervention is more effective as clinicians always want to be able to select the best intervention for patients with FAI. Theoretically, patients with FAI are a series of complex clinical syndromes resulting from the interaction of pathomechanical, sensory perceptual, and motor behavior impairments (19, 20). Balance training alone may only achieve partial therapeutic effects. TCC is a kind of mind–body exercise that may be particularly beneficial to FAI because it involves movement recall, task switching, attention, and visuospatial processing simultaneous with physical movements (21). Therefore, our hypothesis is that both TCC intervention and CBT would obtain significant improvements, with a possible superiority of TCC over CBT. Thus, the aim of this randomized controlled study is to test the comparative effects of TCC intervention and CBT protocols in improving postural balance and subjective instability feelings in patients with FAI.

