## Discussion

Ankle sprain has a high recurrence rate, and repeated sprain often progress into CAI. TCC is an ancient form of physical activity that originated in China and has become widely popular around the world. Even though the benefits of practicing TCC have been proven in different populations, to date there are not enough qualified studies to confirm the clinical effect of TCC exercise on balance ability and ankle instability in subjects with CAI. This study aims to determine the effect of 12 weeks of TCC intervention on postural stability and self-reported outcomes in patients with FAI. At the same time, the superiority of its clinical efficacy will also be compared with that of CBT.

Considering that CAI may limit the sensorimotor system, which may further limit the ability to maintain posture control (27). Commonly used rehabilitation balance programs are reported to improve “proprioception,” which means that they may have a positive effect on the somatosensory system (28, 29). Moreover, as mentioned above, CBT can improve ankle function and increase ankle stability, which has been confirmed by a number of studies (1, 13, 30).

In TCC practice, the slow, gentle, rhythmic movements are connected together in a continuous sequence, and movement transitions, center of gravity shifts, and posture transitions are all closely linked and coherent. These movements challenge the balance control system, which requires the human body to be aware of the body's position and maintain the center of gravity within a changing base of support. Previous studies have indicated that the practice of TCC can effectively improve balance because it can reinforce the sensorimotor system, lower extremity muscle strength, endurance, proprioception, and body awareness (31, 32). In view of the fact that a series of articles have reported that TCC can improve the balance function and other functional symptoms of a variety of populations, including core stability, posture control ability, and lower limb movement ability such as hip, knee, and ankle (16, 32). Thus, we hypothesized that both TCC intervention and CBT would obtain significant improvements of postural stability and self-reported outcomes in patients with FAI.

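### The stated 90% power is not supported for TCC versus CBT: the effect size of 0.8 rests on pre-post data with near-unchanged controls, and 28 per group gives 83.6% two-sided even at 0.8

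*Protocol article*

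**What the plan says.** The protocol article's Sample size section states: "An effect size of 0.8 and a two-sided alpha level of 0.05 were set based on the differences of pre- and post-treatment repeated measurement points"; the measures are SEBT and CAIT. It continues that "a total sample of 56 participants (28 patients in each group) is required to achieve 90% power", and then: "The estimated withdrawal rate was 10–20%, and a total of 68 participants (34 patients in each group) were planned to be enrolled". It describes the powered contrast as the within-group change before and after treatment.

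Two sources are named for the planning data: a published study (reference 18) and the group's own preliminary experiment. The TCC group gained 10.8 CAIT points (SD 2.21) and 6.46 on SEBT-posteromedial (SD 6.89). The SEBT control gain was 0.64 (SD 3.86), and the CAIT control entry reads "CAIT M =0.2, SD = 2.10), with a 1:1 allocation ratio".

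Elsewhere the protocol describes a different comparison:

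- The Background says of the published source that it "failed to compare the clinical effects with other training programs (18").
- The Background also states: "our hypothesis is that both TCC intervention and CBT would obtain significant improvements, with a possible superiority of TCC over CBT".
- The Discussion says that "CBT can improve ankle function and increase ankle stability, which has been confirmed by a number of studies (1, 13, 30").
- Study design and setting gives the objective as the comparison of TCC with CBT. The control arm receives 36 CBT sessions over 12 weeks.

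CAIT is named as the primary measure of functional improvement in its own section. SEBT appears neither in Table 1 nor among the outcome measurements.

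**The concern.** The planning data and the trial have different contrasts. In the planning data, controls barely changed. In this trial, controls receive a training programme that the protocol regards as effective and expects to produce significant improvement. A control gain near zero and a significantly improving control cannot both be the planning assumption for one comparison.

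The preliminary experiment does not resolve this, because its control treatment is not described. If that control was CBT, a gain of 0.2 contradicts the hypothesis that CBT improves patients. If it was something else, the data concern a different comparison.

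What is at stake is the stated power. The article gives no expected TCC-minus-CBT difference and no reason why 0.8 suits an active comparator. A reader will take 90% as the chance of detecting a relevant TCC advantage. A non-significant result would then look more informative than the calculation allows.

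**Working it through.** **Inputs (Sample size section).** Effect size d = 0.8; alpha 0.05 two-sided; 28 per group evaluable, 34 enrolled; CAIT change 10.8 (SD 2.21) versus 0.2 (SD 2.10); SEBT change 6.46 (SD 6.89) versus 0.64 (SD 3.86).

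**1. Reproducing 56 for 90% power.** Two-sample t-test, noncentral t with noncentrality d × √(n/2) on 2n − 2 degrees of freedom.

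- Two-sided, n = 28: noncentrality 0.8 × √14 = 2.99, 54 df, power 83.6%.
- Two-sided, n per group for 90%: 34 (power 90.2%), that is 68 evaluable.
- One-sided 0.05, n = 28: power 90.5%. This reproduces 56 but contradicts the stated two-sided alpha.
- Paired within-group test at d = 0.8: 19 patients give 90%, and 28 give 98.3%. The within-group description therefore does not reproduce 28 either.

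Dropout: 28/0.90 rounds up to 32 and 28/0.80 = 35, so 34 per group lies within the stated 10–20%. The inflation step is sound; the 28 it starts from is not.

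**2. Do the listed figures give 0.8?** d = difference in mean change / √((SD₁² + SD₂²)/2).

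- CAIT: (10.8 − 0.2)/√((2.21² + 2.10²)/2) = 10.6/2.156 = 4.92.
- SEBT: (6.46 − 0.64)/√((6.89² + 3.86²)/2) = 5.82/5.584 = 1.04.

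Neither is 0.8. Entering the CAIT figures directly would require about 3 per group, so the sample size was driven by 0.8 and not by the control gain of 0.2.

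**3. How far does an active control matter on the protocol's own figures?** Keep the TCC gain and pooled SD as listed and let the CBT gain vary. With 28 per group, 90% two-sided power needs d ≈ 0.882.

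- CAIT: 10.8 − 0.882 × 2.156 ≈ 8.9. Power stays at or above 90% until CBT gains about 8.9 points; it is 60.1% at a gain of 9.5 and 27.6% at 10.
- SEBT: 6.46 − 0.882 × 5.584 ≈ 1.5. Power falls below 90% once CBT gains more than about 1.5; it is 83.5% at 2, 62.4% at 3 and 36.7% at 4.

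**4. What the fixed sample size offers for TCC minus CBT.** The protocol states 0.8. The values 0.6, 0.5 and 0.3 are assumptions, because no TCC-versus-CBT difference is given. Two-sided 0.05:

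| d | 28 per group | 34 per group |
|---|---|---|
| 0.8 | 83.6% | 90.2% |
| 0.6 | 59.7% | 68.4% |
| 0.5 | 45.1% | 52.9% |
| 0.3 | 19.7% | 23.0% |

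95% CI half-width with 28 per group: t(54) × √(2/28) = 2.005 × 0.267 = 0.536 SD. That is 1.2 CAIT points at the listed SD of 2.16, and 2.1–2.7 points if the SD is 4–5 (an assumed range).

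**The case against.** The strongest reply is that 0.8 is already far below the listed CAIT effect of 4.92, so it could be a deliberate discount for an active control. The text does not say so. It ties 0.8 to these very differences, and on SEBT 0.8 is only modestly below 1.04. The reply does establish that the gain of 0.2 was not entered directly.

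A second reply is that G*Power's repeated-measures ANOVA could have been used. Its between-group test with f = 0.4 (equivalent to d = 0.8) returns 56 if the correlation between time points is about 0.6 (two time points) or 0.7 (three). No correlation is stated, and that test averages the group difference over all time points, including baseline. The route is possible, but the article does not document it, and it would not justify 0.8 against CBT.

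Third, the trial is described as exploratory, and no equivalence or non-inferiority claim is planned. That lowers the stakes, but the 90% figure is still stated.

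A reader might infer several stronger things that the documents do not support:

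- **The trial will probably be non-significant.** This is not shown. No TCC-minus-CBT difference is given, and on the listed CAIT figures power holds until CBT gains nearly 9 points.
- **The planning controls were untreated, or all figures come from the published study.** A preliminary experiment is also named, and its control is not described.
- **A ceiling shrinks the difference.** CAIT is a 30-point scale and entry is allowed up to 25, so a patient entering above 19.2 cannot gain 10.8 points. No baseline distribution is given, so an effect on the between-group difference cannot be quantified.
- **Three CAIT points is the margin for judging the result.** The protocol gives 3 as a minimum detectable change and does not define it as a between-group margin.

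**Conclusion.** The concern stands in a limited form: the 90% is unsupported for TCC versus CBT. There are two separate reasons. The effect size is attributed to pre-post data with near-unchanged controls, and those data do not produce it. And on the stated d = 0.8 and two-sided alpha, 28 per group gives 83.6%, a shortfall of 6.4 percentage points. The second result assumes a two-sample t-test on one outcome; the first needs no such assumption.

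Whether actual power is high or low cannot be settled from the document. It depends on the CBT gain and on the SD in this population. On CAIT the plan tolerates a large CBT gain if the listed mean and SD carry over; on SEBT it tolerates very little. The enrolled 68 would give 90.2% at 0.8 SD only if nobody were lost, which leaves nothing for the expected 10–20% withdrawal.

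**What to change.** Keep n = 68 and revise the Sample size section:

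1. Remove the within-group contrast and the near-unchanged-control figures as the justification for 90%.
2. State power for TCC minus CBT on CAIT, which the trial measures: 83.6% with 28 per group or 90.2% with 34 per group at 0.8 SD. Add 45% / 53% at 0.5 SD and 20% / 23% at 0.3 SD, labelled as assumptions.
3. Give the expected 95% CI half-width, about 0.54 SD with 28 per group.
4. State that the between-group CAIT difference will be reported with its 95% CI and that non-significance will not be read as equal efficacy.

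The cost is rewording. No extra patients are needed, but the stated power becomes less favourable.
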